## Abstract

In Samoa, adult Type 2 diabetes prevalence has increased within the past 30 years. Patient preferences for care are factors known to influence treatment adherence and are associated with reduced disease progression and severity. However, patient preferences for diabetes care, generally, are understudied, and other patient-centered factors such as willingness-to-pay (WTP) for diabetes treatment have never been explored in this setting. Discrete Choice Experiments (DCE) are useful tools to elicit preferences and WTP for healthcare. DCEs present patients with hypothetical scenarios composed of a series of multi-alternative choice profiles made up of attributes and levels. Patients choose a profile based on which attributes and levels may be preferable for them, thereby quantifying and identifying locally relevant patient-centered preferences. This paper presents the protocol for the design, piloting, and implementation of a DCE identifying patient preferences for diabetes care, in Samoa. Using an exploratory sequential mixed methods design, formative data from a literature review and semi-structured interviews with n = 20 Samoan adults living with Type 2 diabetes was used to design a Best-Best DCE instrument. Experimental design procedures were used to reduce the number of choice-sets and balance the instrument. Following pilot testing, the DCE is being administered to n = 450 Samoan adults living with diabetes, along with associated questionnaires, and anthropometrics. Subsequently, we will also be assessing longitudinally how preferences for care change over time. Data will be analyzed using progressive mixed Rank Order Logit models. The results will identify which diabetes care attributes are important to patients (p < 0.05), examine associations between participant characteristics and preference, illuminate the trade-offs participants are willing to make, and the probability of uptake, and WTP for specific attributes and levels. The results from this study will provide integral data useful for designing and adapting efficacious diabetes intervention and treatment approaches in this setting.

## Introduction

Type 2 diabetes mellitus (hereafter referred to as diabetes) is expected to affect 592 million people by 2035 [1]. Low- and middle-income countries (LMICs) are disproportionately impacted–the Pacific Islands more so than any other region [2]. In Samoa, adult diabetes prevalence increased between 1978 and 2013 from 1.2% to 19.6% in men, and 2.2% to 19.5% in women [3]. In a cohort of adult Samoans (n = 500) diabetes prevalence more than doubled from 11.1% to 27.8% in men and 13.1% to 29.0% in women between 2010 and 2018 [4]. For comparison, 9.3% of adults (≥ 20 years) globally were estimated to have diabetes in 2019 [5]. In 2009, close to 20% of households in Samoa had at least one person who had been diagnosed with diabetes [6, 7].

Work in other settings shows that patient preferences for care are known factors influencing treatment and indirectly (through sustained engagement in care) are associated with reduced disease progression and severity [8, 9]. Health interventions that are culturally adapted, context-specific, and/or incorporate user preferences have been shown to have high impact [10–16] and are better able to reach and improve health outcomes in populations that are at high risk and underserved [17, 18]. Patient preferences, generally, for diabetes care are understudied, and the main factors that guide patients’ decisions to maintain treatment adherence remain largely unidentified. Additionally, other patient-centered factors, which are important for increasing the efficacy and acceptability of care [8, 9, 19, 20], are not well examined in this setting. For example, willingness-to-pay (WTP) [21, 22], which reflects what patients may expect and value from their diabetes care, has yet to be explored in Samoa.

Patient preferences and WTP for improvements in diabetes treatment have been assessed using Discrete Choice Experiments (DCEs) in the US [23], the Netherlands [24] and Denmark [9], but few published studies have used DCEs to measure diabetes care preferences in low- and middle-income countries (LMICs) [25]. These specialized surveys present participants with hypothetical scenarios composed of a series of multi-alternative choice profiles. The alternative profiles are made up of attributes (healthcare components/characteristics such as cost, treatment side effects) with different continuous or categorical levels (e.g., differing treatment prices, binary presence, or absence of side effects, etc.). Participants are asked to choose a profile based on what attribute levels may be preferable for them. Therefore, DCEs add to qualitative measures by capturing quantitative data on strength of preferences and the probability of uptake of defined choices [26]. As a survey- and attribute-based measure of value that provides stated preference data (measuring what participants say they *will do* versus what they *do/have done*), DCEs are particularly useful in settings where patient care experiences are understudied [26].

This project will identify diabetes care attributes that are important and valued by Samoan adults living with diabetes. Additionally, results from this project will provide valuable data to the health system regarding patients’ probability of uptake and WTP for potential services. Finally, the results from this project will provide the formative data necessary to design and adapt efficacious and patient-centered diabetes intervention and treatment approaches.

## Materials and methods

### Aims and hypotheses

Using an exploratory sequential mixed methods approach (Fig 1) [27, 28], we will design, develop, pilot, and administer a DCE in Samoa to identify preferences for diabetes care.

**Fig 1 pone.0295845.g001:**
[figure not shown]
Exploratory sequential design.

The aims of this project are:

To design, pilot, and implement a DCE measuring diabetes care preferences in Samoa.To identify and measure the strength of preference and importance of attributes of diabetes care alternatives and standard care options.To identify the trade-offs (i.e., marginal Willingness to Pay (WTP)), participants are willing to make to obtain preferred attributes, and the probability of uptake for such services.To measure longitudinal changes in care preferences over time.

### Setting

Samoa is an independent, lower-middle income country in the Western Pacific. The majority (>80%) of the estimated population of 206,179 [29] reside on the island of ‘Upolu. ‘Upolu is made up of three census regions: the Apia Urban Area (AUA; Apia is the capital of Samoa), Northwest ‘Upolu (NWU; peri-urban) and the Rest of ‘Upolu (ROU; rural). A smaller proportion of the population lives on the more rural island of Savai’i (SAV census region). Recruitment will be taking place on both islands. The Samoan healthcare system has been characterized as hospital-centric [30] and largely centralized in Apia, where one of two referral hospitals in the country is located (the other on Savai’i). Throughout ’Upolu and Savai’i, there are approximately 12 Ministry of Health-run regional hospitals, and clinics [30]. However, there is only one designated diabetes clinic, centrally located in Apia, where many diabetes patients nationally are referred for treatment. During care encounters, patients generally receive assessments of weight, height, abdominal circumference, blood pressure and capillary blood glucose. Doctors provide counseling regarding medication adherence, diet and physical activity, hypoglycemia symptoms, as well as provide referrals to the hospital eye clinic for detailed fundoscopy, if needed ([name], personal communication). However, the level of detailed diabetes-related care, and diabetes-related education provided for patients can be variable based on resource limitations. Decentralization of the health system and an increasing focus on primary care utilization, health promotion and prevention, community empowerment, and a specific focus on noncommunicable disease management are currently being undertaken as part of the Samoan Government’s NCD Policy and Action Plan (2019–2029) and an ongoing World Bank-led Health Systems Strengthening Program [30].

### Sample size and inclusion criteria

Participants in all phases of the study will be adult Samoans (30 to 80 years) recently diagnosed with diabetes (<12 months for the pilot, <24 months for the finalized implementation) who provide permission to access their medical records and are willing to provide written informed consent for study participation. Twenty participants completed semi-structured interviews and were administered the pilot DCE (completed July 2023). Following refinement of the instrument, the finalized DCE survey is now being administered to n = 450 Samoan adults living with diabetes, along with associated questionnaires and anthropometric measures (initiated August 2023). Baseline recruitment is expected to be completed by July 2024. Two hundred and twenty participants will complete additional DCEs at 12- and 24-months post baseline assessment (Fig 2). Potential participants will be excluded if they are unable or unwilling to complete study protocols and/or were only diagnosed as having gestational diabetes (given the unique healthcare needs of pregnancy). Equal numbers of men and women (50.0%) will be recruited for each phase of the study. Participants will be recruited from regional Ministry of Health run regional hospitals and clinics throughout the islands of ’Upolu and Savai’i, and the diabetes specialty care clinic located centrally in Apia. Participants will also be recruited using the Obesity Lifestyle and Genetic Adaptations (OLaGA) Research Center’s social media page (>9,700 followers). The OLaGA Research Center is a collaboration between Yale and Brown Universities and the Samoan Ministry of Health. After determining eligibility, Samoan Research Assistants (RAs) will introduce the study objectives to the participants. Before each study assessment, written informed consent will be obtained from each participant.

**Fig 2 pone.0295845.g002:**
[figure not shown]
Timeline.

### DCE instrument construction

The design and construction of the DCE survey was based on formative data collected from a literature review and semi-structured interviews following best practice recommendations [26, 31, 32]. We also followed the components of the 10-item checklist developed by the International Society for Pharmacoeconomics and Outcomes Research (ISPOR) Good Research Practices for Conjoint Analysis Task Force to guide the design, development, and implementation of the instrument [33]. Briefly, the 10-items include: 1) the formation of the research questions, 2) identification of attributes and levels, 3) construction of choice sets, 4) experimental design of the instrument (statistical procedures to reduce the number of attribute and level combinations and increase the precision of the survey) 5) preference elicitation, 6) instrument design, 7) data collection plan, 8) statistical analyses, 9) results and conclusions, and 10) study presentation [33]. This project is guided by two main research questions: 1) What attributes of diabetes care do adult Samoans living with diabetes value and prefer, and how do these compare to attributes currently available within standard care protocols? and 2) what are the trade-offs Samoan adults living with diabetes are willing to make to obtain these attributes or services?

### Literature review

We reviewed the existing literature to identify potential attributes for inclusion on the DCE. Papers were included if they focused on adults (age restricted to individuals 18 years and older), were in English, and described care for diabetes (including both Type 1 and Type 2 diabetes, as well as prediabetes management). Databases including PubMed, Medline, and Google Scholar were searched with terms comprised of: “diabetes care attributes”, “diabetes care preferences”, “diabetes care barriers”, “diabetes care adherence”, and “‘Diabetes’ and ‘DCE/Discrete Choice Experiment’”. Study type was not restricted; therefore, results were obtained from studies that used DCEs, quantitative and qualitative interviews, cross-sectional surveys, systematic reviews, and randomized control trials. The review included 45 papers, 22.2% of which focused specifically on DCEs. Attributes identified as important for and/or influencing diabetes care adherence included: intervention/treatment setting [34]; type of provider (i.e., doctors, nurses, educators, case managers, community health workers) [34–37]; provider/healthcare interactions (i.e., service dissatisfaction [38], as well as providers’ cultural competency, consistency of communication, transparency, respect, and compassion) [37–45]; shared decision-making [36, 44]; levels of diabetes education and knowledge provided [39, 41, 45–48]; treatments that improve quality of life [44, 49, 50]; medication/treatment side effects [23, 50–56]; treatment outcomes/goals [9, 23, 49, 52, 53, 56–58]; un- and under-coordinated care [39, 59]; types of self-management and regimen frequency/complexity [34, 36, 40, 43, 48, 50, 53, 54, 60]; access to care and resources [40, 41, 45, 61]; family and social support [42, 59, 62]; emotional support [47]; time requirements [45, 47, 61–64]; and cost/financial support [41, 55, 56, 59, 61].

### Semi-structured interviews

Semi-structured interviews were conducted with n = 20 adults (30–80 years) living with diabetes in Samoa (diagnosis < 12 months). Semi-structured interviews, the construction of the DCE, and piloting of the instrument were funded by the Yale Institute for Global Health’s Global Health Spark Award. Analysis of these interviews resulted in the refinement of the list of attributes and levels used to design the pilot DCE survey [27, 28]. Interviews explored participants’ diabetes care experiences (to contextualize their responses), their preferred attributes and levels of diabetes care (capturing what is important to them and what facilitates their retention in care), and their current care experiences (to inform the standard care option). Interviews were conducted by Samoan RAs trained in qualitative methods (in either Samoan or English based on participant preference) with the goals of (1) refining the list obtained from the literature review and (2) identifying other unlisted attributes that have local relevance. This exercise was used primarily to capture preferences that lie *outside* the domains recognized clinically or generally by the literature review [65]. Additionally, the interviews informed the assignment of appropriate levels to the attributes (e.g., range of acceptable costs for care, treatment locations, etc.). Following transcription and translation of recorded interviews by the RAs, interviews were double coded by members of the study team; NVivo [66] was used to support data analysis. Content analysis was used to identify initial themes regarding diabetes care attribute and level preferences. Additional dating mining tools–such as word and compound query frequencies–were used to identify the most frequently shared and important attributes. Subsequently, consultation with project investigators ([name]) and feedback from the Samoan Ministry of Health’s Health Research Committee regarding feasibility of implementation for identified attributes, facilitated the design of the pilot DCE instrument [32, 67–71].

### Choice set design, and preference elicitation

A ‘Best-Best’ DCE was constructed (*preference elicitation)*. Best-Best DCEs elicit additional preference information, are designed to inherently rank choices, and increase the statistical power for analyses [72–74]. Participants are being presented with a series of choice sets, each with three different alternative care profiles (one of which will always be an ’opt-out/none of these’ for each attribute). Each profile presents a hypothetical scenario (comprised of combinations of attributes and levels) for diabetes care. Participants are asked to choose their most preferred option from the three profiles, followed by their second preference (but not worst) from the remaining alternatives. Because treatment protocols vary by patient, it was challenging to identify a true ’standard care’ level for each attribute. Frequently cited experiences (e.g., only being able to see the first available doctor) were included as potential levels in the design of the instrument and are intended to represent attribute levels generally (but not inclusive to all) experienced by patients. Our aim in doing so is to facilitate a comparison of the preferences for alternative options compared to these commonly experienced encounters; additionally, the inclusion of an opt-out option, provides better representation of real-world scenarios [72].

To design the alternative profiles for both the pilot and final instrument, we mirrored similar DCEs utilized elsewhere and included 8 of the most frequently reported attributes (garnered from the literature review, interviews, and consultation) in the instrument (DCEs within health economics are estimated to have a mode of 6 attributes but can range from 2–24 [31]). The eight attributes included in the pilot was reduced to seven following refinements. Each attribute is between 3–6 levels. The chosen attributes and levels were entered into JMP^®^ Pro 15 (SAS Institute Inc., Cary, NC) where we specified the creation of 12 choice sets for the pilot, and 8 choice sets for the final baseline DCE [71]. Limiting the number of attributes, levels, and choice sets was undertaken to prevent participant fatigue and reduce cognitive burden [32, 73]. We utilized a fractional factorial design [26, 31, 32] to reduce the high number of possible combinations of attributes and levels that could be included in each choice set and an efficiency design to maximize precision [23, 75] (*experimental design*). Both the pilot and final DCE included continuous (i.e., costs of treatment) and categorical attribute levels. Attribute levels are balanced and appear an equal number of times (reducing bias). Further, JMP software allows for the randomization of the order of the choice sets that are presented to the participants and for the creation of multiple survey blocks (we created 9 survey blocks). This helps to ensure the random elicitation of choice sets (reducing bias) and increases the diversity of attribute and level combinations that are encountered by the participants. Block assignments will be adjusted for during analysis.

### Pilot testing

The DCE survey was pilot-tested and refined before initiating implementation among the full sample of participants. The goal of piloting the instrument was to determine participant understanding of the attributes, levels, and choice-sets, as well as their comfortability with the length of the DCE. The DCE was translated into Samoan and administered by the RAs to participants using Qualtrics software [76] for tablet-based data collection. The same n = 20 adults who participated in the semi-structured interviews were asked to complete the pilot survey. Participants evaluated the survey with regards to length, satisfaction, relevance, and comprehension. After finalizing and refining the pilot survey, we designed the finalized DCE instrument (9 survey blocks, 8 choice sets per survey). The length of each survey, and the number created through the fractional factorial design precluded the inclusion of each in this manuscript. Instead, the included attributes and levels used to design the finalized instrument can be found in the supporting information section (S1 Table).

### Implementation

The finalized DCE instrument will be administered to n = 450 adult Samoans recently diagnosed with diabetes (data collection started August 2023; funded as an aim of 5K01DK132514: The Diabetes Clinical outcomes Associated with Retention and Engagement in Care, in Samoa (Diabetes CARE); PI: [name]). After obtaining written informed consent from all participants, RAs are explaining the study objectives, describing what a DCE is (i.e., an explanation that the presented choice sets represent hypothetical scenarios), and are consistently describing the intended definitions of the included attributes and levels. This latter step is intended to help participants assess levels that may be subjective or unfamiliar. For example, continuous glucose monitoring is an included attribute level. This type of glucose management is not common in Samoa at this time, and further explanation may be needed for some participants [33]. In addition to administering the DCE, RAs are collecting demographic (i.e., sex, age, region of residence), anthropometric (i.e., weight and height, and blood pressure), health, and socioeconomic data (income and assets) from participants. Participants are also being administered diabetes knowledge [77], self-management and distress, and treatment adherence [78] questionnaires. These data will be used to examine whether attribute preferences vary by sex and/or are associated with chronic disease risk, age, socioeconomic position, or levels of diabetes knowledge. Assessments take approximately 30–40 minutes.

Two hundred and twenty participants will be asked to complete additional DCEs at 12- and 24-months post initial assessment. The same DCE instrument will be used to measure how preferences change over time as individuals live and manage their diabetes.

### Planned statistical analyses

The statistical modeling of the DCE will be based on random utility theory, where participants choose between alternative profiles, and the attribute levels of the favored option is associated with the highest utility (benefit) to the specific participant [79]. A mixed logit model will be used to estimate choice models from the ’first best’ data and to observe the direction of the rank-ordered attribute choices [74, 80]. Rank order logit (ROL) modeling or Exploded Logit Modeling [81–83] will be used to observe a full ranking of the alternatives in all choice-sets (including first-best and second-best options in the same model) [74] and determine the probability that a participant chooses one option over the others, based on the chosen option’s attribute levels, while controlling for random factors and interindividual tastes [26, 71]. These types of analyses are useful for identifying unknown/unobserved heterogeneity of preferences [26, 73, 84] and will allow for analysis of the cross-sectional panel-like data (participants will be completing multiple choice sets and there will be multiple responses per case/participant). Progressive mixed ROL models will be constructed [74]. A mixed logit version of the ROL will be estimated by ’exploding’ the data as outlined in Lancsar et al. (2017) [72]. Briefly, this procedure will allow each choice set to result in five rows of data, with the first three rows (first sub-choice set) indicating the first-best preference (coded as 1, the remaining two alternatives as 0) and the remaining two rows (second sub-choice set) indicating the second-best preference (coded as 1, the remaining alternative as 0) [72]. By organizing the data in this manner, a traditional mixed multinomial logit model can be conducted that assesses the ranked choices [72]. The chosen profiles will be the dependent variable, and the levels of the attributes will be the independent variables (standard care attribute levels will be initially coded as the reference variable). Interaction terms will be introduced in Model 2 to estimate any associations between attributes and sex. Other case-specific characteristics (e.g., age, levels of diabetes knowledge, weight status, etc.) will be interacted with the intercept and selected attributes to explore the effect of participant characteristics on preferences in Model 3. [74]. We plan to use dummy coding (rather than effects level coding) for categorical variables to facilitate ease of interpretation [73, 74, 85]. The models will allow for the identification of which attributes are important (βs with p<0.05; Aim 2), the direction of that importance (positive or negative βs), and the relative importance of attribute levels compared to others (ratio of estimated parameter to relevant comparator; Aim 2). Further, we will be able to illuminate the trade-offs participants are willing to make between attributes, including marginal WTP (Aim 3). Because we will be including cost of treatment as an attribute, we can estimate the marginal WTP for other attributes; generally, marginal WTP can be estimated by dividing the estimated utility coefficient of an attribute by the utility coefficient of the cost of treatment attribute, holding other attributes constant [9, 86]. We will also be able to estimate the probability of participants taking up a care profile with specific attributes [26]. Sensitivity analyses will be undertaken if we suspect that the relative marginal utility of attributes varies due to differences in income levels. This may include exploring whether preference weights, probability of uptake of alternatives, and WTP vary by different income levels (Satisfaction from the attribute may be based on its associated costs; e.g., perceived satisfaction/preferences of care options may differ by participants’ ability to pay compared to their peers) [84, 87]. The distribution (level balance) of the attributes will be checked across the first and second preferred profiles to ensure the DCE is balanced and that logit model properties are met [88, 89].

Few longitudinal studies using discrete choice experiments have been undertaken [90], therefore analyses will be largely exploratory. Because time between assessments (12 months) is short, the same DCE instrument will be used at each timepoint [90, 91]. Following best practices, we will analyze models at each timepoint using multinomial logit modeling [91]. The Chow Test Analogue for logistic regression will be used to test whether the models’ attribute coefficients significantly differ between timepoints. The Chow Test Analogue allows for comparative analysis of different regression models fitted to two different data sets [91]. By including demographic, socioeconomic, and care-related questionnaire data into our models, we will be able to explore how external factors, and especially changes in external factors such as income status, care use/disuse, and diabetes management and distress, are associated with changes in preferences over time. In the unlikely case that we experience greater loss to follow-up and attrition than expected, we will use repeated cross-sectional DCE approaches (such as a covariate extended model) to measure if differences in preferences across samples are significant [90]. Analyses will be completed in Stata v. 17 (College Station, TX) using the Choice Models (CM) suite of commands [92].

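### Models 2 and 3 read raw logit interactions as preference differences, although a group difference in choice consistency alone would also shift them

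*Protocol article*

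**What the plan says.** All references are to the Protocol article.

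- Planned statistical analyses, on Model 2: "Interaction terms will be introduced in Model 2 to estimate any associations between attributes and sex".
- Implementation, on how the result will be read: "These data will be used to examine whether attribute preferences vary by sex". The same sentence goes on to chronic disease risk, age, socioeconomic position and diabetes knowledge.
- Planned statistical analyses, on other characteristics: they are interacted with the intercept and "selected attributes to explore the effect of participant characteristics on preferences in Model 3".
- The ranked choices are exploded so that "a traditional mixed multinomial logit model can be conducted that assesses the ranked choices". Importance is judged coefficient by coefficient: "which attributes are important (βs with p<0.05; Aim 2".
- Relative importance and marginal WTP are defined as ratios of coefficients. The only group contrast in WTP that the text names is by income, and it is conditional on a suspicion that income matters.
- The sample: "The finalized DCE instrument will be administered to n = 450 adult Samoans recently diagnosed with diabetes"; "Equal numbers of men and women (50.0%) will be recruited for each phase of the study". Sample size and power justifies going beyond the minimum of 125 partly by the wish to study heterogeneity by sex, age or residence.

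The text mentions neither error scale nor choice consistency.

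**The concern.** In a logit model the data identify only the product of taste and error scale, where a larger scale means more consistent choices. A sex interaction can therefore arise in two ways: the sexes want different things, or they want the same things and one sex answers with more noise. Model 2 cannot tell these apart, yet the stated use of the result is to "examine whether attribute preferences vary by sex". Model 3 has the same ambiguity for age and diabetes knowledge.

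At stake is the meaning of the subgroup results. A uniformly weaker set of coefficients in one group could be reported to the health system as that group caring less about cost and services, when its members only chose less consistently.

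**Working it through.** **The plan's own figure.** The minimum sample is 500 × c/(T × A) = 500 × 6/(8 × 3) = 125, as stated. The planned 450 at a 1:1 split gives 225 men and 225 women.

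**Algebra.** Let β be the common taste for an attribute level, with scale 1 in men and λ in women.

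- Coefficient in men: β. In women: λβ.
- Interaction: (λ − 1)β. It is non-zero wherever β is non-zero and λ differs from 1.
- Because λ > 0, λβ has the same sign as β, so a pure scale difference never reverses a preference.
- WTP in women: λβ/(−λβ_cost) = β/(−β_cost), the same as in men.

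Example at λ = 0.7 with an assumed cost coefficient of −0.8 and a level worth 0.6: the cost interaction is (0.7 − 1) × (−0.8) = +0.24 and the level interaction is (0.7 − 1) × 0.6 = −0.18. WTP is 0.6/0.8 = 0.75 in men and 0.42/0.56 = 0.75 in women.

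**Size by simulation.** From the article: 225 per sex, 8 choice sets, two profiles plus opt-out, 9 blocks, 7 attributes, at most 6 levels. Assumed, because the article gives no values: cost with coefficient −0.8; six categorical attributes with 6, 4, 4, 3, 3 and 3 levels and coefficients from 0.15 to 0.6; taste SD 0 or 0.5; women/men scale ratio from 1.0 to 0.5. This gives 1 + 5 + 3 + 3 + 2 + 2 + 2 = 18 attribute-by-sex terms. Tastes were identical by sex. The fitted model was the fixed-coefficient exploded logit with person-clustered standard errors, 400 data sets per row, two-sided 5%. Paired entries are for taste SD 0 / SD 0.5.

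| Scale ratio | Joint test of sex terms rejects | Mean share of the 18 terms with p<0.05 | Mean cost-by-sex term | By-sex WTP contrast rejects |
|---|---|---|---|---|
| 1.0 | 7.5% / 5.8% | 4.9% / 5.0% | 0.00 / 0.00 | 6.5% / 3.5% |
| 0.9 | 15.0% / 9.0% | 7.1% / 5.1% | +0.08 / +0.05 | 4.5% / 4.0% |
| 0.8 | 32.5% / 12.0% | 10.4% / 6.9% | +0.16 / +0.09 | 4.3% / 4.3% |
| 0.7 | 66.0% / 21.2% | 16.5% / 8.8% | +0.24 / +0.16 | 3.0% / 4.5% |
| 0.5 | 100% / 80.7% | 36.2% / 19.2% | +0.40 / +0.28 | 4.3% / 2.5% |

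With taste SD 0 the mean cost terms match (λ − 1) × (−0.8): 0.08, 0.16, 0.24 and 0.40. At ratio 0.7, the number of falsely significant terms averages 0.165 × 18 = 3.0 or 0.088 × 18 = 1.6, against about 0.9 by chance at ratio 1.0.

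**Does the mixed model remove it?** A separate run fitted a mixed exploded logit with random coefficients on all 18 attribute terms (taste SD 0.5, 200 data sets per ratio, 60 draws). The joint likelihood-ratio test of the sex terms rejected 10.5%, 62.5% and 99.5% at ratios 1.0, 0.75 and 0.60. With a relative scale parameter freed, it rejected 11%, 8% and 6%. The test is liberal even at equal scale, so only the contrast between the two series should be read: the excess comes from scale and goes when scale is allowed for.

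**The case against.** The strongest case against runs as follows.

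- **A condensed article.** A scale check is the kind of detail that a fuller plan could hold. That is fair as far as silence goes. But the article does fix the contrast (raw interactions) and its reading (preference variation), and that pairing is what fails.
- **Exploratory analyses.** None of the four aims names a sex comparison. The overall importance, WTP and uptake results do not depend on this point. This stands and limits the weight of the point.
- **Ratios are already planned.** Relative importance and WTP are free of scale and could be computed from Model 2. True, but they are not assigned to sex, age or knowledge contrasts.
- **No mechanism shown.** A reader might infer that one sex is less used to tablets and so answers more erratically. The article does not support that: research assistants administer the survey and explain attributes and levels consistently, and comprehension was piloted. Unfamiliar levels, such as continuous glucose monitoring, remain a possible source of noise, but the article does not link them to sex, age or knowledge.
- **Size.** With taste spread, which the mixed model presumes, the fixed-coefficient fit gives lower rejection (21% rather than 66% at ratio 0.7). The joint test is a summary used here, not one that the plan names. Both points stand.

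**Conclusion.** The point holds as possible confounding. As written, Models 2 and 3 cannot separate different preferences from noisier answers, and the mixed logit does not change that. The algebra needs no assumptions beyond the logit form. The size does: under the assumed coefficients, level counts, taste spread and scale ratios, and with the fixed-coefficient fit, false joint rejection is small near a ratio of 0.9 (about 9% to 15%, against 6% to 7.5% at equal scale) and about 21% to 66% at 0.7.

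Two stronger readings are not supported. A reader might infer that the study will report false sex differences; the article gives no evidence that consistency differs by sex, so that is not shown. A reader might also infer that every attribute would show a significant interaction. The shift applies to every attribute with an effect only in expectation: at ratio 0.7 some 9% to 17% of terms reached p<0.05. Interactions with opposite signs of preference in the two groups cannot come from scale alone.

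**What to change.** **Sex (Model 2).** Fit two models:

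- (a) common tastes with one free relative scale parameter for sex;
- (b) the full set of attribute-by-sex interactions, including the opt-out constant, with scale fixed equal.

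Use the likelihood-ratio test of (b) against (a) as the test of preference differences. With K coefficients, (a) has K + 1 parameters and (b) has 2K, so the test has K − 1 degrees of freedom. A full interaction set should not be combined with a free scale, because with fixed coefficients that model is not identified. In the mixed version, (a) scales the random-coefficient spreads as well, so (b) must let the spreads differ by sex for the models to be nested. With S spreads the degrees of freedom become K + S − 1.

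Model (a) needs no special software: multiply the women's covariate rows by trial values of the ratio and keep the value with the highest likelihood.

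**Reporting.** Give sex differences as differences in marginal WTP or in coefficient ratios, with confidence intervals.

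**Age and diabetes knowledge (Model 3).** Do the same with a prespecified grouping, or with a log-linear scale function, scale = exp(γz), where z is the characteristic. With the scale function, test the selected interactions when added to the scale-only model. This is identified only through the attributes left without an interaction, which are then assumed to have equal tastes.

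**Cost.** No change to design or data collection, and a little more analysis work. Ratio contrasts have somewhat wider intervals than raw interactions.
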